## Abstract

**Background:**

The expeditious surgical evacuation of acute epidural hematoma (AEDH) is an attainable gold standard and is often expected to have a good clinical outcome for patients with surgical indications. However, controversy exists on the optimal surgical options for AEDH, especially for patients with brain herniation. Neurosurgeons are confronted with the decision to evacuate the hematoma with decompressive craniectomy (DC) or craniotomy.

**Methods/design:**

Patients of both sexes, age between 18 and 65 years, who presented to the emergency room with a clinical and radiological diagnosis of AEDH with herniation, were assessed against the inclusion and exclusion criteria to be enrolled in the study. Clinical and radiological information, including diagnosis of AEDH, treatment procedures, and follow-up data at 1, 3, and 6 months after injury, was collected from 120 eligible patients in 51 centers. The patients were randomized into groups of DC versus craniotomy in a 1:1 ratio. The primary outcome was the Glasgow Outcome Score-Extended (GOSE) at 6 months post-injury. Secondary outcomes included incidence of postoperative cerebral infarction, incidence of additional craniocerebral surgery, and other evaluation indicators within 6 months post-injury.

**Discussion:**

This study is expected to support neurosurgeons in their decision to evacuate the epidural hematoma with or without a DC, especially in patients with brain herniation, and provide additional evidence to improve the knowledge in clinical practice.

**Trial registration:**

ClinicalTrials.govNCT 04261673. Registered on 04 February 2020

## Background

Traumatic brain injury (TBI) represents the most challenging global public health care issues, with more than 50 million people suffering from TBI each year worldwide [1, 2]. Acute epidural hematoma (AEDH), a common and severe type of TBI, occurring approximately in 2 to 4% of all TBI patients [3–5], accounts for a substantial proportion of fatal head injuries, with mortality ranging from 1.2 to 33%. AEDH befalls more frequently in young people, with a mean age between 20 and 40 years. Elderly people rarely suffer from AEDH but have a significantly higher mortality. Vehicle-related accidents are the main cause of AEDH, accounting for 53% of all cases (range, 30–86%). Other causes of AEDH, including falls, assaults, and sports injuries, have been reported in several studies [3–5].

Epidural hematomas are caused by bleeding between the outer layers covering the brain and the inner table of the skull. The rapid rise of intracranial pressure (ICP), caused by the mass effect, will result in midline shift and direct or indirect compression of the brainstem. This condition represents a potentially life-threatening emergency and requires prompt diagnosis and neurosurgical intervention. The large availability of computed tomography (CT) scanners for internal examinations facilitates the fast diagnosis of AEDH and allows the monitoring of the disease progression. Thus, the expeditious surgical evacuation of AEDH is an attainable gold standard and is often expected to have a good clinical outcome. Indeed, the treatable nature of epidural hematomas (EDH) has led some surgeons to suggest a “toward zero mortality” as an achievable target for this condition.

Ordinary surgical strategy principally aims to quickly reduce ICP and promote the repositioning of the brain herniation, if concurrent [3]. The Brain Trauma Foundation (BTF) has produced an informative guideline on the surgical indications for AEDH, but no specific surgical options. Although craniotomy for AEDH is conventionally employed in practice, some patients suffered from clinical deterioration by secondary injuries, including fatal cerebral infarction (CI), especially in cases combined with preoperative herniation [3]. In such cases, an initial hematoma evacuation with additional decompressive craniectomy (DC) might effectively prevent and/or alleviate postoperative CI. However, the relatively low incidence of postoperative CI has led few surgeons to opt for the removal of the bone flap in patients with AEDH. In addition, the lack of high-quality evidence regarding the use of decompressive craniectomy in AEDH has determined a great variability in terms of practices between hospitals, countries, and even among surgeons within the same hospital. Other critical issues, such as the proper identification of subgroups that may not benefit from DC, are in need of further exploration. To date, there are no clinical trials that have investigated the validity of decompressive craniectomy in AEDH patients with herniation.

In this research, called Prospective Randomized Evaluation of Decompressive Ipsilateral Craniectomy for Traumatic Acute Epidural Hematoma (PREDICT-AEDH), we present a study protocol for a randomized controlled trial. Our aim is to compare the outcome and cost-effectiveness of DC versus craniotomy in the treatment of TBI patients with cerebral herniation undergoing acute epidural hematoma evacuation.

## Methods and design

### Study design

This is a study protocol for a randomized, multicenter, clinical controlled, pragmatic trial involving 51 neurosurgical centers. Two intervention arms are designed, where patients are allocated in both the craniotomy and DC groups. The patients’ enrollment is expected to be conducted from September 2020 to October 2023 within all the centers involved. All patients are expected to be observed for a total period of 6 months, and the last 6 months’ follow-up assessment will end in May 2024. Clinical information of enrolled participants, including diagnosis of AEDH, clinical radiological information, treatment procedures, and follow-up data, will be collected in detail. A concise flow chart, displaying the overall study design, is shown in Fig. 1. The detailed schedule regarding enrollment, interventions, assessments, and visits for participants is shown in Table 1.

**Fig. 1 Fig1:**
[figure not shown]
Study flow chart

**Table 1 Tab1:** Time schedule of enrollment, interventions, assessments, and follow-up for participants

Time points	Enrollment	Operation and treatment	Follow-up			Adverse effects and other operations
	Day 0	Day 0 to discharge	1 month post-injury	3 months post-injury	6 months post-injury	Within 6 months post-injury
**Informed consent**	**X**					
**Eligibility**	**X**					
**Information of enrollment**	**X**					
**Patient information**	**X**					
**Medical history**	**X**					
**Randomization**	**X**					
**Surgery notes**		**X**				**X**
**Physical and neurological examination**	**X**	**X**	**X**	**X**	**X**	
**Imaging**	**X**	**X**	**X**	**X**	**X**	**X**
**ICP management**		**X**				
**GOSE**		**X**	**X**	**X**	**X**	
**LOS**		**X**	**X**	**X**	**X**	
**Treatment cost**		**X**	**X**	**X**	**X**	
**MMSE**			**X**	**X**	**X**	
**EQ-5D-5L**			**X**	**X**	**X**	

### Participant selection

Patients presenting to the emergency room, with a clinical and radiological diagnosis of AEDH, are eligible for inclusion. The eligible criteria of each patient will be determined by the senior neurosurgeon from each participating center and an external radiologist not involved in the allocation process. This study specifically focuses on patients with unilateral supratentorial epidural hematoma. Herniation here mainly refers to uncal herniation, a common subtype of transtentorial herniation, frequently caused by AEDH located in the temporoparietal and temporal regions. The main criteria to identify uncal herniation are pupillary enlargement and signs of brain stem compression on CT scans.

#### Inclusion criteria

➢ Adults aged ≥ 18 years and ≤ 65 years (18 and 65 are included).➢ With informed consent.➢ Clear medical history of traumatic brain injury.➢ Within 12 h after injury.➢ Acute supratentorial epidural hematoma and signs of brain stem compression on CT scan, representing the leading cause of operation, despite any other minor intracranial injuries associated (e.g., subarachnoid hemorrhage and contusion).➢ The admitting neurosurgeon considers that the epidural hematoma needs to be evacuated with a craniotomy or decompressive craniectomy.➢ Unilateral mydriasis or bilateral mydriasis before the operation.

#### Exclusion criteria

➢ Previous intracranial surgery before trauma.➢ Patients with a Glasgow Coma Score of 3, with bilateral fixed and dilated pupils, bleeding diathesis or defective coagulation, or other injuries that were deemed to be unsurvivable.➢ Patients who had an injury to the oculomotor nerve.➢ Patients are considered to be operated mainly due to the following pathological changes on CT: subdural hematoma, intracerebral hemorrhage, large size infarction, etc., but not because of epidural hematoma.➢ Severe pre-existing disability or severe co-morbidity leading to a poor outcome even if the patient is supposed to have a good recovery from the TBI.➢ Pregnant female.

### Sample size calculation, randomization, and blinding

Our data and results from a previous retrospective study are showing that almost all the patients who received a synchronous DC (93%) had a GOSE of 6.63 ± 1.27, with a favorable outcome (defined by the GOSE categories: lower moderate disability, upper moderate disability, lower good recovery, and upper good recovery). Patients who received craniotomy had a GOSE of 5.78 ± 1.58, with a favorable outcome in 72% of the patients [6]. We calculated the sample required in this clinical trial with a significance level of 5% (two-sided) and a power of 80% to demonstrate the difference in the rate of favorable outcome, with an assumption that 10% of the patients would be lost during follow-up. Ultimately, considering the quality of the study, the sample size is enlarged to 120.

All participating centers must have a neurosurgical on-call team and an emergency department responsible for the admission of head-injured patients to identify eligible patients. After recording the patient’s clinical information, including Glasgow Coma Scale (GCS), pupillary reactivity, and CT findings, an electronic data collection (EDC) database will generate the subject identification number that will be allocated to the eligible patients. A secure central web-based randomization management information system will be used for the randomization of eligible patients. The system will provide an immediate allocation along with the patient randomization record number for the trial, and individual randomization record numbers can be checked at any time. Blocked randomization will be used, with a block size of 4 and an allocation ratio of 1:1. The 24-h central web-based randomization management information system will be backed by one delegated person (available 24 h per day) who will assure the cover-up of the record allocation. The delegated person responsible for randomization will not be involved in the treatment procedure. A confirmatory email will be sent to the investigator of each center involved to verify the allocation.

A patient who is randomly allocated to the craniotomy group, but finally receives a decompressive craniectomy as a lifesaving action during the initial surgery, will be rejected from this randomized controlled trial. This potential selection bias is beyond the control of the investigators, and according to the current guidelines, no specific surgical options are provided for the enrolled participants. Nevertheless, patients’ detailed data will be recorded, providing the observational cohort information necessary to further analyze the possible factors and potential bias.

Due to the nature of the intervention, and the risk that DC surgical procedure will result in skull defect, patients and treating doctors cannot be blinded to allocation. However, the evaluators involved in this study and the investigators responsible for the outcomes’ analysis are blinded to the groups.

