### Implementation and data management

A Trial Management Committee (TMC), including chief investigators from each site, clinical research associates (CRA), the ethics committee and institutional review board, and treatment representatives, is established to ensure a proper implementation throughout the trial process. The chief investigators will be responsible for ensuring adherence to the study protocol, compliance with the consent process, follow-up, and accurate data collection. The trial coordinating center, authorized by TMC, will report all the enrollment records and schemes every month and will monitor the recruitment phase and assess the trial progresses in collaboration with the clinical investigators. A research summary conference will be held every 6 months to evaluate progresses and discuss possible solutions to the problems that may arise.

All data will be collected and recorded using CRFs and the EDC; a data management committee (DMC, located at Clinical Research Institute, Shanghai Jiaotong University School of Medicine) will be established to develop and maintain the EDC and supervise the data quality. Monitoring and auditing will be performed against the original documentation on a monthly basis by the CRA of DMC. Regular visits will be scheduled in each participating center to ensure the compliance with the research program requirements. In case of anomalies, the CRA will promptly submit the information to the investigators in order to find a solution.

All investigators participating in this study will comply with the requirements of the Data Protection Act 1998 concerning the collection, storage, processing, and disclosure of personal information. Access to collated participant data will be restricted to approved individuals involved in the treatment process and representatives from regulatory authorities. Computers used to input data will set up user names and passwords with limited access measures. Published results will not contain any personal data that could allow the participants’ identification. All study documents will be kept for a minimum of 5 years, and documents will not be destroyed without permission from the leading research center when the minimum retention period has elapsed.

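### A single fixed block size of 4, published during recruitment of an unblinded surgical trial, is a minor and cheaply avoidable weakness in allocation concealment

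*Protocol article*

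**What the plan says.** The section on sample size, randomisation and blinding fixes the block length: "Blocked randomization will be used, with a block size of 4 and an allocation ratio of 1:1". No other length is mentioned, and nothing is said about stratification by centre.

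The same section describes the safeguards. "A secure central web-based randomization management information system will be used for the randomization of eligible patients". The system is backed by a delegated person outside the treatment team "who will assure the cover-up of the record allocation".

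On blinding, it states that "patients and treating doctors cannot be blinded to allocation"; outcome evaluators and analysts are blinded.

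One inclusion criterion is a surgical judgement: "The admitting neurosurgeon considers that the epidural hematoma needs to be evacuated with a craniotomy or decompressive craniectomy". Under Participant selection, eligibility is determined by the centre's senior neurosurgeon together with an external radiologist who takes no part in allocation.

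Trial status gives recruitment as September 2020 to a planned end in October 2023, with the current protocol version dated 8 February 2021. The block length was therefore set out in an article written while patients were still being entered.

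**The concern.** In an unblinded trial, past allocations are visible to those who treat the patients. If the block length is also known and never varies, past allocations can reveal the next one: once two patients in a block of 4 have gone to the same arm, the rest of the block is settled. Central allocation hides the upcoming assignment inside the system, but it does not prevent this inference by someone who holds the history.

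At stake is selection before randomisation. A surgeon who knew or could guess the next arm might put a patient forward or hold one back according to a belief about who needs decompression. The Background reports wide variation in practice, even among surgeons in one hospital, so such beliefs are plausible. Blinded outcome assessment does not address this bias, and analysis cannot reliably repair it.

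**Working it through.** The plan gives no predictability figure to reproduce, so the shares are derived from its block size and ratio.

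**Inputs.** Block of 4 at 1:1, and 120 patients (Sample size calculation, randomization, and blinding); 51 centres (Study design).

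**1. Observer who knows the whole preceding sequence, fixed block of 4.** There are 6 balanced sequences.
- Positions 1 and 2 are never determined.
- Position 3 is determined if the first two arms agree, with probability 1/3.
- Position 4 is always determined.
- Certain share: (0 + 0 + 1/3 + 1)/4 = 33.3%, which is 40 of 120 patients.
- Best-guess accuracy: (1/2 + 2/3 + 2/3 + 1)/4 = 70.8%, against 50% with no predictability.

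**2. Surgeon who sees only own-centre allocations, one unstratified central list.** Assume that all centres recruit equally and independently and, generously, that the surgeon knows where each block starts.
- The next arm is certain only if both earlier same-arm patients of that block came from this centre.
- Certain share: 1/3 × (1/51)² = 0.013%, or about 0.015 of 120 patients.
- For a centre that recruits 20% of the trial (an illustrative value): 1/3 × 0.20² = 1.3% of its own allocations.

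**3. Surgeon who sees only own-centre allocations, blocks run within centre.** This layout is an assumption. The mean is 120/51 = 2.4 patients per centre, so many blocks never fill.
- Perfectly even recruitment: 18 centres with 3 patients and 33 with 2 (54 + 66 = 120). Only third patients can be certain: 18 × 1/3 = 6, and 6/120 = 5%.
- Random recruitment at equal rates (simulated): about 15%.
- Uneven recruitment (simulated with centre shares from a Dirichlet distribution, parameter 1.0, 0.5 and 0.3): about 20%, 22% and 24%.

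**4. Effect of varying the block length.** These results are simulated on lists of 120 patients. The observer knows the whole history and the set of lengths, but not the length of the current block.

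| Block lengths | Certain | Best-guess accuracy |
|---|---|---|
| 4 only | 33% | 71% |
| 4 and 6 | about 5.5% | 69% |
| 4, 6 and 8 | about 2% | 68% |

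The gain is almost entirely the removal of certain allocations. Guessing better than chance remains possible for this observer.

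**The case against.** The strongest answer is that the observer behind the one-third figure does not appear in the document. Allocation is central, a person outside treatment guards it, and 120 patients are spread over 51 centres. A typical site sees two or three allocations in about three years. On an unstratified list it could not follow the sequence. This stands, and it is why one third cannot be taken as the size of the problem.

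A reader might infer from three sentences that allocations travel between sites. The documents do not support that.
- "A confirmatory email will be sent to the investigator of each center involved to verify the allocation" most naturally means the centre concerned, which already knows the arm.
- "individual randomization record numbers can be checked at any time" speaks of record numbers and does not mention other sites' arms.
- The coordinating centre "will report all the enrollment records and schemes every month", but the text names no recipient and does not say that arms are shown.

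Access rights and stratification are also details that an article commonly leaves to the full protocol, so silence on them is not evidence of a leak.

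Entry is constrained as well. The external radiologist shares the eligibility decision, the criteria require mydriasis and brain stem compression on CT, and the judgement quoted above is about the need for evacuation by either operation, not about the arm. Within 12 hours of injury and with herniation, there is little room to time entry. What remains possible is not putting a patient forward, because a patient who is never proposed is never reviewed.

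None of this defends a single published block length as such. It limits how much the choice matters.

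**Conclusion.** The point holds as a cheap improvement of low severity. The fixed, published block of 4 is stated in the text, and it leaves more predictability than is needed in a trial where surgeons know past arms and have some say over entry.

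Its size depends on what a recruiter can see. One third of allocations are certain only with the full preceding sequence, and no recruiter is shown to have that. With own-centre knowledge only, the share is near zero on one central list (about 0.01% under equal recruitment) and roughly 5% to 24% with within-centre blocks, depending on how uneven recruitment is. The document does not settle which layout is used.

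It would be too strong to conclude that a third of allocations are actually known to surgeons, that concealment has been broken, or that the trial's results would be biased.

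**What to change.** For patients not yet randomised, generate the remaining list with block lengths that vary at random (for example 4, 6 and 8). The randomisation service alone should hold the lengths and should not disclose them to sites or in public documents until recruitment ends. The protocol sentence can then say that block lengths vary and will be reported after recruitment closes.

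The cost is a regenerated list in the existing web system and a short protocol change, which the article says must first go to the review board. The statistical price is a larger possible imbalance if recruitment stops partway through a block: up to 4 patients on a list instead of 2. No extra patients or data are needed. If recruitment has already ended, there is nothing left to change.

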### Data collection

Once patients are enrolled in the study, data related to demographic and clinical information, including hospital admission, treatment process, and follow-up, will be collected by the local investigators and recorded on the case report form (CRF). Detailed data consisting of neurological condition, timing of injury (also the ER, initial CT, and surgical operation), radiographic abnormalities, operation data, and postoperative care management (including ICP management and pharmacological data) will also be recorded. Postoperative CT scan will be performed routinely on the 1st, 3rd, and 7th day post-initial surgery. Cerebral infarction will be initially detected by postoperative CT image depicting a low-dense area. The blood supply of involved lobes will be further detected by transcranial Doppler sonography (TCD) and/or MR. Follow-up visits in the outpatient department are scheduled at 1, 3, and 6 months after injury; data will be collected and recorded. The information recorded on CRFs will be entered into an electronic data collection (EDC) database by a designated person within each participating center. A subject must be withdrawn from the trial if one of the following applies:
Each patient or his/her legally authorized representative has the right to require withdrawal from the study cohort for any reasons after enrollment.The investigator will withdraw a patient who is randomly allocated to a craniotomy and that eventually requires a DC as lifesaving action during the initial surgery.In addition, the investigator could withdraw the patients from their allocated treatment group if a clinical reason for not performing the surgical intervention is identified after randomization.Lost to follow-up.

The primary reason for all discontinuations and withdrawals will be documented.

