So far, there is no reliable data able to clarify the potential selection bias caused by the number of patients who, after initial allocation to a craniotomy, eventually require a DC. This study aims to be a pragmatic trial to improve and specify the surgical options for AEDH. Data of patients who, after initially undergoing craniotomy, eventually require a DC will be recorded, as the incidence of additional craniocerebral surgery after the initial surgical treatment (secondary endpoint). All these information will help in evaluating the potential selection bias.

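### Rejecting craniotomy patients who are converted to DC during the first operation removes randomised patients from one arm only, so the GOSE comparison no longer compares the groups as randomised

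*Protocol article*

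**What the plan says.** The rule appears twice in the protocol article. Under *Sample size calculation, randomization, and blinding*, a patient allocated to craniotomy "but finally receives a decompressive craniectomy as a lifesaving action during the initial surgery, will be rejected from this randomized controlled trial". Under *Data collection*, in the list of cases that must be withdrawn, the investigator "will withdraw a patient who is randomly allocated to a craniotomy and that eventually requires a DC as lifesaving action" during the initial operation. Neither section has a matching conversion rule for the DC arm.

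The same list has a second, optional route that is open to both arms: "the investigator could withdraw the patients from their allocated treatment group if a clinical reason for not performing the surgical intervention is identified after randomization".

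The article acknowledges the problem. It states: "This potential selection bias is beyond the control of the investigators". It adds that "patients’ detailed data will be recorded, providing the observational cohort information necessary to further analyze the possible factors and potential bias". Under *Data analysis* it concedes that "there is no reliable data able to clarify the potential selection bias caused by the number of patients who, after initial allocation to a craniotomy" is followed by a DC. That section also describes the purpose: "This study aims to be a pragmatic trial to improve and specify the surgical options for AEDH". It sets out an ordinal logistic regression of GOSE but does not bring the rejected patients back into it. No section says that all randomised patients are analysed as allocated.

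**The concern.** Whether a craniotomy patient stays in the trial depends on something that happens after allocation, during the operation, and plausibly linked to prognosis. A patient with the same operative course who was allocated to DC simply receives the allocated operation and is counted. The comparison becomes all DC patients against the craniotomy patients in whom the bone flap could be replaced. The treating doctors are not blinded, so the decision that removes a patient is made with knowledge of the arm. Blinded outcome assessment cannot correct that.

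The question of a pragmatic trial, which allocated strategy gives the better 6-month outcome, is then not answered. A real advantage of DC could be understated, or an advantage of craniotomy could appear that does not exist.

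The conversion itself may be outside the investigators' control. Leaving the patient out of the analysis is not: it is a choice of the plan. Keeping the data as an observational cohort does not restore the randomised comparison. Nor does the secondary endpoint that *Data analysis* offers as help. *Aims and outcomes* defines it as further surgery for deterioration after the initial operation, so it misses conversions during that operation.

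**Working it through.** **Inputs from the article** (*Sample size calculation, randomization, and blinding*): favourable outcome 93% with DC and 72% with craniotomy; two-sided 5% level; 80% power; 10% loss; 1:1 allocation; 120 patients.

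**The plan's own figure.** With pooled variance and mean rate (0.93 + 0.72)/2 = 0.825, n per arm = [1.96·√(2·0.825·0.175) + 0.8416·√(0.93·0.07 + 0.72·0.28)]² / 0.21² = 50.2, so 51 per arm and 102 in total. Dividing 51 by 0.9 gives 57 per arm, 114 in total. The article does not state its figure before enlargement; 114 enlarged to 120 is consistent with its text. Evaluable patients: 60 × 0.9 = 54 per arm.

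**Assumptions not in the documents.** c is the share of the craniotomy arm that is converted (5 to 20%). f is the favourable rate among converted patients (30 to 60% for power, 30 to 50% for false positives). The 72% is taken as the rate in all patients allocated to craniotomy. The binary endpoint used for sizing stands in for the ordinal analysis.

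**Formula.** After rejection the craniotomy rate becomes (0.72 − c·f)/(1 − c), in 54·(1 − c) patients. The bias is c·(0.72 − f)/(1 − c). Example with c = 10%, f = 30%: (0.72 − 0.03)/0.90 = 76.7%, so the gap of 21 points becomes 16.3.

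**Power**, by exact enumeration of the pooled chi-square test. Without rejection (54 v 54) it is 85.0%; the usual normal approximation gives 83%.

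| c | craniotomy n | f = 30%: rate, gap, power | f = 60%: rate, gap, power |
|---|---|---|---|
| 5% | 51 | 74.2%, 18.8 points, 77% | 72.6%, 20.4 points, 82% |
| 10% | 49 | 76.7%, 16.3 points, 67% | 73.3%, 19.7 points, 80% |
| 20% | 43 | 82.5%, 10.5 points, 37% | 75.0%, 18.0 points, 70% |

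**Direction.** At f = 72% the bias is zero. At f = 93%, the article's DC figure, it reverses: 0.10 × (0.72 − 0.93)/0.90 = −2.3 points at c = 10%, and 0.20 × (−0.21)/0.80 = −5.3 points at c = 20%.

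**False positives** (two-sided, no true difference, same enumeration). The common true rate p replaces 0.72 in the formula. Ranges run from f = 50% to f = 30%.

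| c | p = 72% in both arms | p = 82.5% in both arms |
|---|---|---|
| 5% | 5-6% | 6-7% |
| 10% | 6-8% | 8-13% |
| 15% | 7-14% | 13-29% |

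The excess over 5% falls on the side of craniotomy. With c = 10%, f = 30% and p = 82.5%, 12.9 of the 13.2 percentage points favour craniotomy.

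**Other reading of the 72%.** The article gives 72% for patients who received craniotomy. If it already describes patients who completed one, it is the rate left after rejection and only n falls: 54 v 49 gives 83.8% power (c = 10%) and 54 v 43 gives 80.5% (c = 20%).

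**The case against.** A reader might infer that the worst cases, those with brain swelling, are removed and that the trial is therefore known to be biased toward craniotomy. The documents do not support that as fact. They do not mention swelling in this rule and give no outcomes for converted patients, who do receive DC. The only hint of a poorer prognosis is that the conversion is described as lifesaving. The direction must stay conditional.

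A reader might also take a fall in power from 85% to 67% or 37% as following from the plan's figures. It does not. Those values need an assumed conversion rate, an outcome at the poor end of the assumed range, and the reading of 72% as an as-randomised rate. On the other reading, planned power hardly moves. The false-positive rates depend just as much on the common rate chosen.

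The authors disclose the potential bias and record the data, so nothing is concealed. The conversion rule is also not the only withdrawal after randomisation, since the optional route covers both arms.

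These objections limit what can be said about direction and size. They do not restore the comparison. Nor is this a detail left to an analysis plan that is not shown: the article states the exclusion twice, once as mandatory. Even with an unknown direction, the analysed groups are not those that were randomised.

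**Conclusion.** The rule is wrong as written and should be changed before the primary analysis, because it acts directly on the primary endpoint. This conclusion needs no assumption about outcomes. The exclusion follows randomisation, applies to one arm and is triggered by unblinded surgeons, and nothing in the article returns these patients to the GOSE comparison.

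The size is not known. Under the stated assumptions it runs from slight (power 77-82% at 5% conversion) to serious (37-70% at 20%), and the error rate with no true difference rises at 10% conversion to 6-8% or 8-13%, depending on the common rate. If 72% already describes completed craniotomies, the planned power is about 84% at 10% conversion and 80% at 20%, but the result still does not estimate the effect of the allocated strategy.

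**What to change.** - Delete the rejection rule under *Sample size calculation, randomization, and blinding* and the matching withdrawal item under *Data collection*.
- Reword the item that lets investigators withdraw patients for a clinical reason, so that it ends the allocated treatment only, not follow-up or analysis. Otherwise a second route out of the randomised comparison stays open.
- State that the primary analysis includes all randomised patients in their allocated arm, except where consent to use data has been withdrawn, as *Ethics and dissemination* provides.
- Collect 6-month GOSE on converted patients. Confirm that the detailed data already promised for them include it; the article does not say so.
- Restore patients already rejected under the rule, where data and consent allow.
- Report departures from the allocated surgery by arm, and keep the analysis without converted patients as supplementary.

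The cost is a protocol amendment, revised analysis wording and, if it is not already planned, a 6-month assessment of converted patients. No extra patients need to be randomised. The surgeon's decision during the operation is unchanged; only the analysis population and follow-up are affected.
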